### Intervention

All participants will be provided with the patient educational booklet 'Whiplash injury recovery: A self management guide' published by the Motor Accident Insurance Commission (Queensland)[18], which provides information about whiplash, advice on symptom management and illustrates a simple exercise program. Participants will be randomised to one of two groups. Participants in Group 1 will receive 6 treatments of combined dry-needling and exercise delivered in the first 3 weeks of the 6 week program, and 4 treatments of exercise only in the last 3 weeks of the program. Participants in Group 2 will receive an identical protocol, except that a sham dry-needling technique is used instead of dry-needling.

Sham dry-needling uses needles which cause a pricking sensation when pushed against the skin. The needle disappears into the handle with increased pressure. This mechanism invokes a similar sensation to that produced by dry-needling, which includes the non-specific effects of clinician -therapist contact and explanation, as well as the perception that the needle is entering the skin, although sham dry-needling is proposed to have less physiological effect than true needling[19]. Needling sites will be dependent on findings by the physiotherapist following assessment for the presence of hyperalgesia on palpation. Only posterior muscles of the cervical spine and upper thoracic spine will be treated whilst the participant is lying prone, to ensure the participant remains blinded to the needling group allocation. Examples of posterior muscles which may be treated are the trapezius, levator scapulae, splenius capitus, semispinalis and spinalis capitis muscles.

The 6-week exercise program will be carried out under supervision from the physiotherapist and will comprise specific exercises to improve the movement and control of the neck and shoulder girdles (see Table 1). The exercises will be tailored by the physiotherapist for each individual participant, are of a low load nature and are designed to be pain free. At the same time, the physiotherapist will guide the subject's return to normal activities. This programme is similar to those utilised by physiotherapists in clinical practice and has been used in previous studies[5].

**Table 1 T1:** List of Exercises

Exercise	Description

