### Outcome Measures

Age, gender, time since injury, compensation status, previous treatments and medication usage for the whiplash condition will be obtained at baseline. The assessor administering the outcomes will be blind to the group allocation of the participant. Outcome measures will be assessed at baseline, 6, 12, 24 and 52 weeks after randomization.

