### Secondary outcome measures

3. Average pain intensity over last week (Visual Analogue Scale)[21]

4. Average pain intensity over last 24 hours (Visual Analogue Scale)[21]

5. Patient-generated measure of disability (Patient-Specific Functional Scale)[22]

6. Whiplash-specific measure of disability (Whiplash Disability Questionnaire) [23]

7. Generic measure of health status (SF-36) [24]

8. Measures of physical impairment (Cervical range of movement, pressure pain threshold, cold pain threshold) [25]

9. Impact of events scale (IES) [25]

10. Pain Catastrophising Scale (PCS)

11. Posttraumatic stress Diagnostic Scale (PDS)

12. Self report Leeds Assessment of Neuropathic Symptoms and Sign (S-LANSS Pain Score)[25]

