### Adverse Events

All adverse effects, defined as any negative or unwanted reactions to the interventions will be recorded. These will include increased pain (greater than 2 points the VAS scale for greater than 1 week), skin infection, skin irritation or any other reported physical discomfort. An adverse effects committee (chaired by MS) will manage any adverse reactions as they occur. Adverse effects of treatment will be identified using open-ended questioning at the 6 week follow-up assessment.

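### The only stated harm enquiry is at week 6, as the programme ends, so a pain rise starting in its last 7 days cannot meet the plan's own duration criterion and no later visit is stated to ask again

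*Protocol article*

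**What the plan says.** All references are to the protocol article.

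- **Adverse Events, scope:** "All adverse effects, defined as any negative or unwanted reactions to the interventions will be recorded". A committee "will manage any adverse reactions as they occur".
- **Adverse Events, what counts:** the list is inclusive. It names "increased pain (greater than 2 points the VAS scale for greater than 1 week" and ends with "skin infection, skin irritation or any other reported physical discomfort".
- **Adverse Events, how and when harms are found:** "Adverse effects of treatment will be identified using open-ended questioning at the 6 week follow-up assessment". No other identification step is given.
- **Intervention:** needling or sham needling is confined to the first 3 weeks of a 6-week programme. It is followed by "4 treatments of exercise only in the last 3 weeks of the program", in both groups.
- **Outcome Measures:** "Outcome measures will be assessed at baseline, 6, 12, 24 and 52 weeks after randomization". The secondary outcomes measured then include "Average pain intensity over last week (Visual Analogue Scale".

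**The concern.** The article chose to state when and how harms are identified, so this is more than a detail left to a fuller document. The chosen time falls at the end of treatment, and the named pain harm needs more than a week to declare itself. A reaction to one of the last sessions therefore cannot be classified under the trial's own rule when the question is asked. A reaction still present at week 6 has no stated follow-up, although participants return three more times. At stake is how complete and how well classified the harm data are, mainly for late reactions to exercise and for any reaction that persists. Benefit would be described to 52 weeks beside harms actively asked about once.

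**Working it through.** The plan gives no figure on this point to reproduce, so the check is one of timing.

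**Inputs**
- Visit: 6 weeks after randomisation, 6 × 7 = day 42 (Outcome Measures).
- Pain criterion: duration greater than 7 days (Adverse Events).
- Programme: 6 weeks, 42 days; needling or sham in the first 21 days; 4 exercise-only sessions in the last 21 (Intervention).
- Interval from randomisation to first treatment, k days: not stated. I take k = 0 as the base case and k = 7 as an illustration.

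**Step 1: longest duration observable at the visit.** With k = 0 this is 42 − onset day.

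| Onset day | Longest observable duration (days) | Can exceed 7 days? |
|---|---|---|
| 21 | 21 | yes |
| 28 | 14 | yes |
| 34 | 8 | yes |
| 35 | 7 | no |
| 36 | 6 | no |
| 42 | 0 | no |

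The span in which the criterion cannot be met is the last 7 of 42 programme days: 7 / 42 = 17%.

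**Step 2: delayed start.** If treatment starts k days after randomisation, the visit falls on programme day 42 − k and the span widens to 7 + k days. For k = 7 it is 14 days, 14 / 42 = 33%, and the last 7 of those days fall after the visit. Conversely, a visit held v days late narrows the span to 7 + k − v.

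**Step 3: sessions affected.** The article gives no spacing. If the 4 late sessions are evenly spread, there is one per 21 / 4 = 5.25 days. Then 7 / 5.25 = 1.3 of the 10 sessions (13%) fall in the span for k = 0, and 14 / 5.25 = 2.7 of 10 (27%) for k = 7.

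**Step 4: does it touch the needling weeks?** Needling ends about day 21, which leaves 42 − 21 = 21 days before the visit, or 14 days if k = 7. Both exceed 7, so a pain rise that begins during the needling period can meet the criterion by week 6. The affected span holds exercise-only sessions, planned identically for both arms.

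**Step 5: after week 6.** From week 6 to week 52 is 46 of 52 weeks (88%) with no stated harm enquiry. This describes the schedule; it does not estimate missed events.

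**The case against.** The strongest reply is that the article does not say what a quick reading suggests.

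- **A reader might infer that harm recording closes at week 6.** The text does not support that. The promise to record all adverse effects and the committee's remit to manage reactions as they arise carry no end date. Both leave room for spontaneous reports, for instance at supervised sessions. What stands is narrower: week 6 is the only identification step stated.
- **A reader might infer that late pain rises are lost.** They need not be. A rise reported at week 6 can be entered as other physical discomfort. It misses the named pain criterion, and if it later passes 1 week nothing is stated that would reclassify it.
- **A reader might infer that later pain worsening is excluded as a harm, or that the trial could not show whether participants end up worse.** Neither follows. Harms are defined as reactions to the interventions, so a higher VAS at 12 to 52 weeks would not qualify automatically. VAS pain and the −5 to +5 global recovery scale are measured at every follow-up visit and can show worsening.
- **The gap bears little on the needling question.** This is correct for the final week (step 4). However, the definition covers reactions to the interventions, and exercise is one of them. A needling reaction that persists beyond week 6 also has no stated follow-up.
- **A journal article commonly leaves safety logistics to the full protocol.** That is fair for the committee's procedures and data feed. It does not answer a stated time point at which a stated criterion cannot be applied to the final week.

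**Conclusion.** The point holds in a limited form. The single stated enquiry, at the end of treatment, cannot apply the plan's own duration criterion to pain rises that begin in the last 7 of 42 days (17%), and no later visit is stated to ask again or to record whether an effect persisted. This assumes that treatment starts at randomisation and that the visit is on day 42. A delayed start widens the span day for day, and a late visit narrows it. The session shares of 13% and 27% also need even spacing, and the 27% an assumed 1-week delay. The consequence is some misclassified late reactions and no stated outcome for persisting ones, with little effect on the needling-versus-sham harm comparison. It is worth correcting because the remedy is cheap and would bring the method closer to the stated aim of recording all adverse effects.

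**What to change.** In Adverse Events:

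1. Repeat the same open-ended question at the existing 12-week visit, and preferably at 24 and 52 weeks.
2. At each visit, record the current status of any effect that was unresolved at the previous one.
3. Report harms by group and visit.
4. Optionally, tabulate by group the participants whose last-week average VAS is more than 2 points above baseline, labelled as a description of worsening and not as attributed harms.

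The cost is a few minutes at visits already scheduled; the optional table uses data already collected. The drawback is that later reports will include the natural fluctuation of whiplash pain, for which the sham group gives a comparison.

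### Adverse effects are to be managed as they arise, but the only stated way of finding them is open-ended questioning at week 6, which cannot reliably establish the plan's own pain criterion

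*Protocol article*

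**What the plan says.** Three statements in the Adverse Events section of the protocol article bear on this point.

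- Scope: "All adverse effects, defined as any negative or unwanted reactions to the interventions will be recorded". The listed examples are "increased pain (greater than 2 points the VAS scale for greater than 1 week), skin infection, skin irritation or any other reported physical discomfort".
- Handling: an adverse effects committee "will manage any adverse reactions as they occur".
- Detection: "Adverse effects of treatment will be identified using open-ended questioning at the 6 week follow-up assessment". No other route or time is stated.

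Elsewhere in the article:

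- The Intervention section puts all 6 needling or sham sessions in the first 3 weeks of a 6-week programme, followed by 4 exercise-only sessions in the last 3 weeks.
- Outcome Measures gives the visit schedule: "Outcome measures will be assessed at baseline, 6, 12, 24 and 52 weeks after randomization". It also says: "The assessor administering the outcomes will be blind to the group allocation of the participant".
- Under Secondary outcome measures, pain is scored on two VAS items, one described as "Average pain intensity over last week (Visual Analogue Scale" and the other covering the last 24 hours.

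**The concern.** The handling sentence and the detection sentence do not fit together. A reaction first identified at week 6 cannot have been managed when it happened. The detection method is also weaker than the definition it serves: the definition is numerical in size and duration, while the method is unstructured recall with no VAS reading behind it for the period when needling takes place.

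What is at stake is mainly safety information. Brief or mild reactions to needling are easily forgotten after several weeks, so counts are likely to be too low, and the committee may hear of them late. There is a secondary, conditional issue. The questioning takes place at the visit where a blinded assessor administers outcomes. The Discussion says the sham needle does not enter the skin, so a report of a reaction that implies skin penetration could hint at true needling.

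**Working it through.** The plan gives no figure on this point to reproduce. The check sets its sentences side by side and works out the timing.

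**Inputs**
- Needling or sham: 6 sessions in weeks 0 to 3; exercise only: 4 sessions in weeks 3 to 6 (Intervention).
- Stated detection time: week 6 (Adverse Events).
- VAS times: baseline, then weeks 6, 12, 24 and 52 (Outcome Measures). Longest recall window: 1 week (Secondary outcome measures).
- Pain criterion: a rise of more than 2 VAS points lasting more than 1 week (Adverse Events).
- Assumption: treatment starts close to randomisation, so programme weeks and follow-up weeks coincide. If it starts *d* weeks later, the recall intervals in step 1 shorten by *d*.

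**Step 1. Delay from exposure to questioning**
- Last needling: 6 − 3 = 3 weeks.
- First needling: 6 − 0 = 6 weeks.
- Treatment contacts before the question: 6 + 4 = 10.

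**Step 2. What the scheduled VAS covers**
- The week-6 last-week item covers 6 − 1 = week 5 to week 6, which is 1/6 = 17% of the programme.
- The gap between the end of needling and the start of that window is 5 − 3 = 2 weeks.

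**Step 3. Which flares have no scheduled reading**
- A flare starting at week *s* and over by week 5 has a duration of at most 5 − *s*.
- For *s* = 0 that is up to 5 weeks; for *s* = 3 it is up to 2 weeks.
- Both limits exceed the 1 week in the criterion. So a qualifying flare after any needling session, including the last, can begin and end with no scheduled VAS value.
- A flare persisting into weeks 5 to 6 would raise the week-6 score. But one reading with a one-week window cannot by itself show a duration of more than 1 week, so that part still rests on recall.

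**Step 4. What session-level readings would add**
- If sessions are evenly spaced, the interval is 3/6 = 0.5 week in the needling phase and 3/4 = 0.75 week afterwards.
- A flare of more than 1 week then spans at least 1/0.5 = 2 readings if it falls within the needling phase. Within the exercise-only phase it spans at least 1 (1/0.75 = 1.33, rounded down). Where only one falls inside the flare, duration still needs the participant's own account.

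**Step 5. Blinding**
- Stated: the outcome assessor is blind; the questioning is at the week-6 assessment; the sham needle pricks without entering the skin.
- Not stated: who asks the question, and whether before or after outcomes are measured.
- The risk therefore exists only if the assessor asks, asks before the measurements, and hears something that points to skin penetration.

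**The case against.** The strongest reply is that the section does not say week 6 is the sole route. It mentions reported discomfort and handling as reactions arise, which suggests that participants can tell the physiotherapist during the programme, with systematic questioning added at week 6. Session forms are operational detail that a journal article may leave to the full protocol. This stands in part. A reader might infer that nothing is recorded at any of the 10 sessions, or that detection is a single question; the article says neither. What remains is that the one route and time it does state conflict with the handling sentence beside it.

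Three other inferences go further than the document allows.

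- *Pain flares cannot be observed at all.* A participant may remember a flare and report it, and one still present at week 6 would affect the scheduled score. The supportable statement is that a resolved flare has no scheduled reading to verify it.
- *The assessor will be unblinded.* The text does not say who asks or in what order, and the sham also pricks, so irritation or soreness can occur in both arms. If the risk arose, it would bear mainly on the examiner-dependent secondary measures (cervical range of movement, pressure and cold pain thresholds). The two primary outcomes, the Neck Disability Index and global impression of recovery, are patient-reported.
- *The safety comparison is biased towards no difference.* No event rate or capture rate is given. If the same fraction *f* of reactions were captured in both arms, with true risks *p1* and *p0*, the observed difference would be *f*(*p1* − *p0*). That is smaller in absolute terms but leaves the ratio unchanged. With unequal capture the direction is unknown.

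**Conclusion.** The point holds as an internal inconsistency and a weak method of ascertainment. The stated detection route comes about 3 to 6 weeks after the needling or sham sessions and does not fit the promise to handle reactions as they arise. The numerical pain criterion cannot be reliably established for a flare that resolves before about week 5, because no VAS lies between baseline and week 6. Brief reactions are likely to be under-counted; by how much cannot be worked out from the document. Unblinding is a conditional risk, not a stated consequence.

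This rests on treatment starting near randomisation and on the article's stated route being the main one. If the full protocol already provides for recording at each session, the remaining task is to correct the wording. The efficacy analysis of the primary outcomes is not called into question. It is worth changing because it affects the safety comparison and the committee's oversight, and correction is cheap.

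**What to change.** 1. Reconcile the sentences in the Adverse Events section, so that they state when and how adverse effects are identified, how the VAS criterion is ascertained, and who collects the answers. How a reaction is then managed clinically is for the investigators; no rule is proposed here.
2. Add a short standard form at the 10 existing treatment sessions, completed by the participant and identical in both arms: the categories already listed, a pain VAS and one open question. Forward it to the adverse effects committee when completed.
3. Keep the open-ended week-6 questioning, but collect it after all outcomes on a sealed self-completed form that the blinded assessor does not see. It should not go through the independent research assistant, who administers the allocation schedule (Randomisation).

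The cost is a little extra form-filling at visits that already take place, with no added visits. The drawback is that the forms are handed out by physiotherapists who know the arm; self-completion and a fixed layout limit their influence.

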### Randomisation

Participants will be randomly allocated to groups by concealed allocation. A statistician who is independent of the study will be responsible for generating the computerised randomisation schedule. An independent research assistant will administer the schedule and perform all communication between participants and treating practitioners.

### Sample size calculations

The NDI was used to determine sample size, as previous clinical trials have shown this variable to have a smaller effect size than the measure of perceived recovery [5]. The minimal clinically important change for the NDI is 7 points [26] with a conservative standard deviation of 18 based on previous work[5,27]. Based on 80% power at *p *= 0.05, 54 participants will be required in each group. Allowing for a 10% loss to follow up, a total of 60 participants will be required in each group, with 120 participants in total.

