### Data management and analysis

All analyses will be conducted on an intention to treat basis. The outcomes measured at 6, 12, 24 and 52 weeks will be analysed using linear mixed and logistic regression models that will include their respective baseline scores as a covariate, subjects as a random effect and treatment conditions as fixed factors. Age, gender, duration of condition and IES scores will be included as covariates in the analysis. Regression diagnostics will be used to check for normality of the measures and homogeneity of variance as appropriate. Alpha will be set at 0.01.

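### The sample size inputs (7 NDI points, SD 18, 80% power, p = 0.05) do not yield 54 per group; an unadjusted two-group comparison needs 105

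*Protocol article*

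**What the plan says.** The section Sample size calculations gives a complete calculation. The effect and spread are stated as "The minimal clinically important change for the NDI is 7 points [26] with a conservative standard deviation of 18", the SD being drawn from earlier work. The result is then given: "Based on 80% power at" p = 0.05, "54 participants will be required in each group". A 10% allowance for loss raises this to 60 per group and 120 in total, the number that also appears in the Abstract and under Participants. The section does not say whether the test is one- or two-sided. It mentions no correlation between baseline and follow-up, no variance reduction and no gain from repeated measurements.

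The section Data management and analysis plans linear mixed and logistic models for the outcomes at 6, 12, 24 and 52 weeks. These models will "include their respective baseline scores as a covariate", together with age, gender, duration of the condition and IES score. It ends with "Alpha will be set at 0.01", which differs from the level used for the sample size.

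**The concern.** Every quantity needed for a standard two-group calculation is printed, and the printed answer is about half of what those quantities require. This is not a detail that a condensed article leaves to a fuller document: a result is stated, and it does not follow from its stated inputs. The planned total of 120 rests on it.

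At stake is the claim of 80% power for the difference the protocol itself calls minimally important. For the comparison as written, the chance of missing a true 7-point difference is close to one half. The stated power would therefore mislead anyone who uses it to judge how informative a non-significant result is.

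**Working it through.** **Inputs.** From Sample size calculations: difference δ = 7 (read as a between-group difference on the 0–100 scale), SD = 18, power 80%, alpha 0.05, loss 10%. From Data management and analysis: alpha 0.01, baseline score as covariate. Assumed: two-sided testing unless noted, and the correlations in step 4.

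**1. Trying to reproduce 54.** For two independent groups, n per group = 2(z₁₋α/₂ + z₀.₈)² (SD/δ)².

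- Two-sided 0.05: 2 × (1.960 + 0.842)² × (18/7)² = 2 × 7.849 × 6.612 = 103.8, so 104. The t-test gives 104.8, so **105**.
- One-sided 0.05: t-test 82.4, so **83**.
- Two-sided 0.01: t-test 156.1, so **157**.

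None of these is 54. The one-sample or paired formula drops the factor 2: 7.849 × 6.612 = 51.9 by the normal approximation and **53.85** by the t-test, which rounds up to 54.

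The loss step is sound: 54/0.9 = 60. The same step applied to 105 gives 116.7, so 117 per group.

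**2. Unadjusted power for 7 points.** At 54 per group the standardised difference is (7/18) × √(54/2) = 0.389 × 5.196 = 2.02. Against a critical value of 1.96, power is Φ(2.02 − 1.96) ≈ 52%; the t-test gives 51.7%. If all 60 per group are analysed, it is 56%. At two-sided 0.01, power is about 28% with 54 per group.

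**3. Difference detectable with 80% power, 54 per group, SD 18.** By the normal approximation at two-sided 0.05: 2.802 × 18 × √(2/54) = 9.7. The t-test gives 9.8 points at two-sided 0.05 and 12.0 points at two-sided 0.01.

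**4. Credit for the baseline covariate.** If 18 is the unadjusted SD at follow-up, adjustment reduces it to 18√(1 − ρ²). For one follow-up time and 54 per group (t-test):

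| Assumed ρ | Residual SD | Power, alpha 0.05 | Power, alpha 0.01 |
|---|---|---|---|
| none | 18.0 | 52% | 28% |
| 0.5 | 15.6 | 64% | 39% |
| 0.6 | 14.4 | 71% | 46% |
| 0.7 | 12.85 | 80% | 58% |

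At two-sided 0.05, a correlation of about 0.70 is therefore what single-timepoint adjustment needs to make 54 sufficient. The article states no correlation.

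**The case against.** The strongest reply is that the planned analysis is not an unadjusted t-test. It is a mixed model with baseline and other covariates over four follow-ups, and such a model can need far fewer participants. That is correct. A baseline correlation of 0.70 at two-sided 0.05 reaches 54, and it is not the only route. A one-sided 0.05 test with a correlation of 0.6 needs about 53 per group. A baseline-adjusted mean of two follow-ups, with all correlations 0.5, also needs about 53. A baseline-adjusted mean of all four, with baseline correlation 0.5 and 0.7 between follow-ups, needs about 55. All these correlations are assumptions. None of these routes appears in the sample size section, so they do not repair its wording, but they do mean that the paired-formula explanation cannot be taken as established.

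It is also fair that the article is condensed and the sources for SD 18 are not visible. Whether 18 is a cross-sectional SD or the SD of a change cannot be settled here. If it is an SD of change or a residual SD, the covariate gain in step 4 may not be available.

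A reader might infer from the entry rule of NDI at least 28/100 that truncating baseline weakens the covariate gain. That does not follow: selection on baseline lowers the correlation but also shrinks the follow-up SD, leaving the residual SD unchanged (12.85 for an unselected correlation of 0.7 and SD 18). Power would fall only if 18 is already the SD after selection, which the article does not say.

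**Conclusion.** The stated inputs do not yield the stated sample size. An unadjusted two-group comparison needs 105 per group two-sided or 83 one-sided, against 54 printed; at 54 per group its power is about 52% at two-sided 0.05. This rests on reading 7 points as a between-group difference and 18 as the SD in each group. Coincidence with the one-sample size of 53.85 is a plausible cause and no more.

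A reader might go further and say that the trial has 52% power. The document does not support that. The 52% belongs to the calculation as printed, not to the planned analysis, whose power depends on correlations that are not given and on which alpha governs. At one follow-up time, with correlations from 0.5 to 0.7, adjusted power runs from 64% to 80% at 0.05 and from 39% to 58% at 0.01. Under the analysis section's own alpha, even a correlation of 0.7 at a single timepoint falls well short of 80%. The paragraph needs correcting because the trial's size is justified by it and the correction is cheap.

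**What to change.** Keep 120 participants and restate the Sample size calculations paragraph.

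1. Reconcile the 0.05 there with the 0.01 in Data management and analysis, and state whether the test is two-sided.
2. For 54 evaluable per group and SD 18, give the unadjusted power for 7 points and the difference detectable with 80% power under the chosen alpha: about 52% and 9.8 points at two-sided 0.05, or about 28% and 12.0 points at two-sided 0.01.
3. If credit is taken for the baseline covariate or the repeated follow-ups, state what the SD of 18 refers to, the assumed correlations, their source and the resulting power, preferably over a range such as 0.5 to 0.7.

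A sentence saying that a non-significant result will be read by whether the confidence interval excludes 7 points would be useful but is optional.

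The cost is rewording the sample size paragraph, aligning the alpha statement and accepting a less favourable stated power. No further participants are needed for the correction.
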